### Exploratory analyses

Subgroup analyses will be undertaken to examine the role of variables that may contribute to risk factors associated with POCD, such as demographic information, health and medical history, socioeconomic status, and other data collected during the study. These subgroup analyses can be examined using a multilevel modelling approach. For example, by treating the presence of POCD in a participant as an outcome level, it will be possible to examine the relative contributions of each independent variable to POCD (e.g. varying treatment effects for differing levels of demographics). This approach can also be expanded to further examine other participant outcomes, such as the presence of delirium, mood dysfunction, or a significant change in quality of life. For exploratory analyses focussed upon proportionate data, such as comparisons of dichotomous delirium or mood dysfunction outcomes, McNemars’ test can be used to examine within-groups differences across time points. The role of perioperative pain upon POCD may also be explored as a potential cognitive trajectory modulator.

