## Background

Cognitive decline after surgery is common amongst elderly surgical patients [1–3]. Postoperative cognitive dysfunction (POCD) refers specifically to dysfunction in postoperative cognitive performance relative to presurgical performance; however, the exact threshold delineating when cognitive decline can be classified as POCD varies considerably within the literature [4]. One of the most robust studies places the early postoperative incidence rate of POCD at approximately 25 % of major surgery patients, aged over 60 years [1, 3, 4], and research suggests that patients aged at least 60 years are at significantly greater risk compared to younger patients [37]. Generally, cognitive decline after surgery manifests as subtle dysfunction across a number of cognitive domains, such as memory, attention, and psychomotor function. It may persist in some patients for months or years and herald the onset of a dementia process, to the significant detriment of quality of life [5–8]. Given the lack of consensus regarding the exact demarcation of POCD, it is useful to refer instead to an absolute difference in cognitive function after surgery controlling for baseline values, regardless of whether or not such a change in function meets the specifications for POCD.

At present, there are neither pharmacological interventions nor preventative agents for POCD. The role of oxidative stress and neuroinflammation as a result of a surgical stress response is well-characterised, and now provides a potentially modifiable target for therapeutic intervention [9–13]. Developing evidence suggests that there is a relationship between surgery and anaesthesia and the production of inflammatory signals and reactive oxygen species in the periphery and the brain which are associated with cognitive dysfunction [14–19].

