Stratification by age enhances parity between groups in terms of its effects upon cognition, in accordance with established risk factors [5, 37]. Despite the relative safety and success of orthopaedic operations compared with nonorthopaedic operations, the risk of cognitive dysfunction is still significant [3]. Accordingly, orthopaedic patients represent an opportunity to examine potential cognitive change that is less likely attributable to other factors. Additionally, stratification by orthopaedic and nonorthopaedic counteracts the wide variability of reported POCD in the literature [38]. Meta-analyses suggest small cognitive improvements from pooled data yet individual studies note an incidence of POCD as high as 45 % [38]. It is widely held that this variability is due mostly to discrepancies in diagnostic criteria [39] but the concern remains that a significant subset of individuals within the orthopaedic cohort do experience cognitive improvement. The literature to date has not provided the means to identify them prospectively, but it has been suggested that a low cognitive baseline secondary to chronic inflammation, pain, opioid consumption, and restricted mobility, coupled with the potential for surgical remedy, is a potent confounder of postsurgical cognition [40]. This complex and not yet fully characterised surgical profile suggests that the broad classification of surgeries into orthopaedic and nonorthopaedic may help to minimise any confounding in the collected data, with negligible loss of power with respect to a nonstratified design.

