
### Primary analysis

The primary study hypothesis states that the perioperative administration of NAC is superior to placebo in reducing the severity of postoperative dysfunction, as measured by the CBB at POD 7, and compared with baseline. Analysis of the primary outcome will be via ANCOVA, utilising the baseline psychomotor-attention composite score as a covariate. Assumptions of the ANCOVA will be examined through standard tests and residual plots, with transformation of variables being considered if normality of the residuals is not met. The psychomotor-attention composite is made up of the detection and identification tasks on the CBB and represents the reaction time of the participant, where higher scores indicate lower reaction speed and can be used to suggest the presence of impairment. The composite score is calculated by standardising each task score and adding them together. All analyses will be performed as intent-to-treat, in order to best emulate practice settings.

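### The exploratory predictor and subgroup models are illustrated with POCD present or absent, although the protocol prefers the baseline-adjusted continuous change and already collects it

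*Protocol article*

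**What the plan says.** The Background of the protocol article notes that "the exact threshold delineating when cognitive decline can be classified as POCD varies considerably within the literature". Because there is no consensus, it says "it is useful to refer instead to an absolute difference in cognitive function after surgery controlling for baseline values", and adds that this applies "regardless of whether or not such a change in function meets the specifications for POCD".

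The secondary aims include finding what predicts change in cognition after surgery. The section on assessments and information lists the demographic and medical variables gathered for that purpose.

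The primary outcome is continuous. Under Primary analysis, "The composite score is calculated by standardising each task score and adding them together", and the score is analysed by ANCOVA with its baseline as covariate. Under Secondary analyses, the individual battery tasks are also analysed by ANCOVA and linear mixed models.

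The Exploratory analyses section turns to risk factors and states: "These subgroup analyses can be examined using a multilevel modelling approach". Its worked example is to proceed "by treating the presence of POCD in a participant as an outcome level", in order to judge the contribution of each variable and whether treatment effects differ across levels of demographics. It then says the approach can be extended to other participant outcomes such as delirium or mood dysfunction. No continuous cognitive score is named as an outcome for these models, although the last sentence of the section also mentions pain as a possible modulator of cognitive trajectory.

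**The concern.** The Background gives a reason for working with graded change: the POCD threshold is not agreed. The aim is written in the same terms. The one example given for the predictor and varying-treatment-effect models goes back to the classification that the Background chose not to rely on.

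This is more than terminology. Reducing a continuous score to yes or no treats a participant just beyond the cut like one far beyond it, and one just short of it like one who did not decline at all. The loss falls on risk-factor associations, which may be modest, and on arm-by-covariate interactions, which have less power than main effects to begin with. The continuous scores are measured anyway, so nothing is gained in data collection by giving up that information.

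**Working it through.** **1. Reproduce the plan's own figure.** Inputs from Sample size determination: effect 0.255 SD, pre/post correlation 0.5, alpha 0.05 (taken as two-sided), power 80%, 1:1 allocation.

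n per arm = 2 × (1.960 + 0.842)² × (1 − 0.5²) / 0.255² = 2 × 7.849 × 0.75 / 0.0650 ≈ 181.1, rounded up to 182, so N = 364. The protocol states 370; at 185 per arm the power is 0.808. The stated size is therefore that of an ANCOVA on the uncut score, and it is reproduced within 2%.

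**2. Information kept when a normal score is cut.** Let p be the proportion classed as POCD, z the normal quantile at 1 − p, and φ the normal density. For small effects, the efficiency of the binary outcome relative to the uncut score is

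E(p) = φ(z)² / [p(1 − p)].

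Sources for p: the Background puts the "early postoperative incidence rate of POCD at approximately 25" per cent; the section on randomisation reports that "individual studies note an incidence of POCD as high as 45" per cent, in its discussion of orthopaedic surgery. The 10% is an assumption standing for a stricter cut, and 50% is the most favourable cut possible.

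| p | z | φ(z)² / [p(1 − p)] | Kept | Lost | 370 act like | Needed to match 370 |
|---|---|---|---|---|---|---|
| 10% (assumed) | 1.282 | 0.0308 / 0.0900 | 0.342 | 66% | 127 | 1081 |
| 25% (Background) | 0.674 | 0.1010 / 0.1875 | 0.539 | 46% | 199 | 687 |
| 45% (orthopaedic studies) | 0.126 | 0.1567 / 0.2475 | 0.633 | 37% | 234 | 585 |
| 50% (best case) | 0 | 0.1592 / 0.2500 | 0.637 | 36% | 236 | 581 |

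**3. Check on a predictor model.** In a simulation with n = 370, one normal predictor correlated 0.15 with the outcome (an assumed value) and 1500 runs per setting, the power of linear regression on the uncut score against logistic regression on the cut score was:

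- p = 10%: 82% against 38%
- p = 25%: 83% against 59%
- p = 45%: 80% against 62%

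The linear figure should not depend on p; its variation is simulation error. The formula agrees. The linear test statistic is centred near 0.15 × √370 / √(1 − 0.15²) = 2.92, giving power Φ(2.92 − 1.96) = 0.83. Multiplying by √0.539 gives 2.14, and power Φ(2.14 − 1.96) = 0.57.

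**4. Check on a treatment contrast.** This is an illustration, not a planned test. The planning effect on the baseline-adjusted scale is 0.255 / √0.75 = 0.294 SD. With 25% POCD on placebo, the rate on NAC would be Φ(−0.674 − 0.294) = 16.6%. At 185 per arm, power is 81% for the continuous score and 51% for 25% against 16.6%. For 80% power, N is 364 against 738.

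**The case against.** The strongest reply is that the section commits to little. It is headed as exploratory, says that the models can be used, and offers POCD as an example. The primary and secondary between-group cognitive analyses stay continuous. The Background can also be read as a choice of terms: the primary hypothesis itself speaks of the severity of early POCD as measured by change on the composite, so the protocol sometimes uses the word for graded change. All of this stands, and it limits the weight of the point. It does not remove it, because a stated secondary aim concerns predictors and this is the only place where models for them are described.

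Four stronger readings are tempting, and the documents do not support them.

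- A reader might infer that the predictor analyses are bound to a binary outcome. The wording is permissive, so they are not.
- A reader might object that no POCD cut-off is given. This is a journal article, and a definition may stand in the full protocol or an analysis plan that is not shown. Nor does the point need it: a well-defined cut-off would lose information too.
- A reader might say that a multilevel model is impossible with one yes/no result per participant. The section names no single visit, and cognition is tested on day 7 and at 3 and 12 months, so repeated status within participants could supply a second level.
- A reader might divide the expected number of cases by the number of listed variables and call the model overfitted. That needs the same rate in both arms and all variables entered in one model; the protocol states neither.

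**Conclusion.** The point holds as an inconsistency in an exploratory section, with a better method available from data already collected. The Background and the secondary aim point to graded change adjusted for baseline; the worked example points to POCD status.

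The size is conditional. A loss of about 46% applies if POCD is a cut of a roughly normal continuous score and 25% of participants fall beyond it. Under the same model the loss is 37% at 45% and 66% at an assumed 10%, and no cut does better than 36%. The 25% and 45% are literature rates, and the protocol says that no literature examines the CBB for detecting POCD, so the rate in this trial could differ. A reader might infer a fixed loss of half the information; the documents do not say that POCD would be cut from the composite. If it were classified from the whole battery, the formula would not compare like with like.

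The primary result, the secondary between-group comparisons and the sample size of 370 are untouched. This is a worthwhile correction of modest weight.

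**What to change.** Reword the Exploratory analyses section as follows.

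1. The outcomes of the predictor models are the continuous cognitive scores, each adjusted for its own baseline. The day-7 psychomotor-attention composite comes first, with the RBANS, COWAT, Trail Making and remaining CBB scores alongside. The other scores are needed because the composite rests on two reaction-time tasks, and using it alone would narrow an aim that is about cognition more broadly.
2. Subgroup effects are tested as arm-by-covariate interactions in the same ANCOVA, reported as estimates with confidence intervals and labelled exploratory.
3. Any classification of POCD is kept as a supplementary display.

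This changes analysis wording only: no new data, visits or participants. The downside is that results are slightly less comparable with papers that report POCD rates, which the supplementary display largely covers. Reporting several scores side by side also means more exploratory results, to be read together and not singled out.

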### Missing or incomplete data

All participants recruited into the study, regardless of treatment group, are to have as much data as possible recorded, as fully as possible in accordance with this protocol. Missing data is monitored so as to avoid bias by attrition or patterns of missing data. All cases of missing data, including instances of nonretention of participants or withdrawal of consent, are to be recorded by research staff. Where data is missing, the frequency and reasons for missing data are to be recorded. Missing data is to be examined to see if there are patterns informative to the study; for example, if certain variables are missed in a systematic way by an identifiable pattern of participant.

In situations where data is missing, for example with participants who are lost to the 12-month follow-up, the data collected up to that point should still be used provided the participant has not withdrawn their consent or requested that the information be removed. If missing data is considered Missing at Random (MAR, i.e. without a pattern), then multiple imputation methods should be used to estimate missing values. The accepted minimum number of imputations is five, to estimate the missing data from existing data. This can be achieved using statistical software. If data appears to be missing in a way that is not random (Missing Not At Random, MNAR), then this data can be examined for potential biases or patterns statistically, and missing values can then be estimated using monotonistic methods.

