The literature suggests a strong correlation between the two tasks of the psychomotor-attention composite, detection and identification, for simplicity’s sake assumed to be in the region of *r* = 0.8 is expected (for example, see the similarities present on scores from the research of Hammers et al., 2012; [55] and Lim et al., 2012 [56]). Further, the variances for pre and postsurgery will be standardised to 1. The variance of the composite is calculated as the sum of pre and postsurgical variances plus twice the correlation of the composite tasks; 2 + 2 (0.8) = 3.6. Therefore, to estimate the effect of MCI (and by extension, cognitive change after surgery), we divide the combined effect size for the psychomotor-attention composite by the standard deviation of the effect size, that is the square root of the variance of the composite. From Lim et al., the effect of MCI size of the change in reaction speed for the detection and identification tasks were −0.33 and −0.63, respectively, giving a total reduction in reaction speed effect size of −0.96. Therefore, the total effect of MCI (and by extension, cognitive change after surgery) upon the psychomotor-attention composite is equal to: −0.96/√3.6 = −0.51. Given that NAC is unlikely to improve cognition beyond baseline estimates, it is proposed that NAC may instead ameliorate the severity of cognitive dysfunction compared with placebo. Given the limited available data, we have attempted to estimate an approximate protective effect based on the use of NAC in analogous conditions, such as traumatic brain injury [63]. Additionally, it is unrealistic to assume complete prevention of cognitive dysfunction. Therefore, a relative reduction in severity of cognitive dysfunction of 50 % represents an appropriate compromise to calculate the power. Given the likelihood of significant correlation in pre and postsurgery cognition scores, and in the absence of any identifiable correlation size, it is prudent to include an estimation of correlation patterns in the medium range (*r* = 0.50). A protective effect of NAC of 50 % would then set the expected effect of postoperative cognitive change as modulated by NAC at = −0.255. Assuming an alpha level of 0.05, power of 80 %, and a pre and postsurgical score correlation of 0.5, a sample size of 370 participants will have 80 % power to detect a minimum absolute effect size of 0.255 using an analysis of covariance (ANCOVA) model. This sample size includes approximately equal representation across stratification by age and surgery type for intervention.

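### The missing-data rule misdefines MAR, selects the method by a test the data cannot provide, and answers MNAR with an undefined method

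*Protocol article*

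**What the plan says.** The section 'Missing or incomplete data' sets a two-branch rule. The mechanism is first judged from the data: "Missing data is to be examined to see if there are patterns informative to the study". The example given there is of gaps concentrated in a recognisable type of participant.

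- **First branch:** "If missing data is considered Missing at Random (MAR, i.e. without a pattern), then multiple imputation methods should be used to estimate missing values". The number of imputations has a floor: "The accepted minimum number of imputations is five".
- **Second branch:** "If data appears to be missing in a way that is not random (Missing Not At Random, MNAR), then this data can be examined" for biases or patterns, after which "missing values can then be estimated using monotonistic methods". The article does not define that last term.

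The rule reaches the primary endpoint. Under 'Primary analysis' the article says "All analyses will be performed as intent-to-treat, in order to best emulate practice settings", and the day-7 model is given as "Analysis of the primary outcome will be via ANCOVA, utilising the baseline psychomotor-attention composite score as a covariate". No section of the article fixes one missing-data method in advance or names an analysis under an MNAR assumption.

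**The concern.** The rule has three faults, all in its wording.

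1. **Definition.** Missingness without any pattern is MCAR. Under MAR, missingness may depend on anything recorded, such as age, surgery type, baseline score or arm. That is the situation in which multiple imputation is most useful, yet the gloss sends such data out of the multiple-imputation branch.
2. **Trigger.** Observed data can contradict MCAR. They cannot separate MAR from MNAR, because the two differ only in how missingness relates to values nobody has. A rule that turns on whether data appear to be MNAR leaves the choice of method to judgement after the data have been inspected.
3. **Remedy.** *Monotonistic* most naturally means monotone imputation. Monotone describes the shape of the missing-data pattern, and in its usual form the method still assumes MAR. On that reading the MNAR branch gives no sensitivity to MNAR.

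The article gives reasons to expect missing day-7 scores that are not purely accidental. 'Discussion' names attrition as a limitation and says nausea and vomiting may lead to withdrawal, which could differ by arm. 'Withdrawal' lists further surgery or anaesthesia before the primary measurement among the grounds for withdrawal from treatment and/or assessment. What is at stake is whether the conclusion on the primary endpoint can be shown to withstand plausible departures from MAR.

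**Working it through.** **The design figure, for scale.** 'Sample size determination' gives "Assuming an alpha level of 0.05, power of 80 %, and a pre and postsurgical score correlation of 0.5", with standardised variance 1, effect 0.255 and 370 participants in all. With two-sided alpha (assumed; the article does not say):

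n per arm = 2 × (1.960 + 0.842)² × (1 − 0.5²) / 0.255² = 2 × 7.849 × 0.75 / 0.0650 ≈ 181.1, rounded up to 182.

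That is 364 in total, against 370 stated; power at 185 per arm is 0.81. The figure reproduces, and nothing below changes it.

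**Following the rule on one case.** Suppose day-7 scores are missing more often in participants with poor baseline scores.

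- By the standard definition this is MAR if baseline accounts for the missingness, and multiple imputation is suitable.
- By the article's gloss there is a pattern, so the multiple-imputation condition fails.
- The only other branch is the MNAR one, with an undefined method.

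If missingness also depended on the unseen day-7 score, the observed data could look the same. Inspection cannot settle which case holds.

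**Size of an MNAR departure (assumed inputs).** Let f be the fraction missing in an arm and δ the amount by which the true missing scores are worse than MAR predicts. An MAR-based estimate of that arm's mean is off by f × δ, and the NAC-minus-placebo contrast is off by f(placebo) × δ(placebo) − f(NAC) × δ(NAC).

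- One arm only, f = 0.10, δ = 0.3: 0.10 × 0.3 = 0.03; 0.03 / 0.255 = 12%.
- One arm only, f = 0.10, δ = 1.0: 0.10 × 1.0 = 0.10; 0.10 / 0.255 = 39%.
- Equal f and δ in both arms: the two terms cancel.

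Higher composite scores are worse, so a true contrast of −0.255 would be estimated as −0.225 to −0.155 if the problem lay in placebo, and as −0.285 to −0.355 if it lay in NAC.

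**Illustrative simulation.** 370 participants, correlation 0.5, SD 1, 2,000 runs, 20 regression imputations of the day-7 score. The mechanisms are assumed.

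| Missingness | Missing | True effect | MI estimate | 95% CI coverage |
|---|---|---|---|---|
| Depends on arm and baseline (MAR, clear pattern) | 18% | −0.255 | −0.253 | 0.956 |
| Depends on outcome, placebo only (MNAR) | 14% | −0.255 | −0.129 | 0.74 |
| Depends on outcome, both arms alike (MNAR) | 15% | −0.255 | −0.229 | 0.944 |

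With a true effect of 0 and the placebo-only mechanism, the estimate was +0.133 and the test rejected in 29% of runs. The first row shows that patterned data can be MAR and handled well by imputation. The second shows that monotone regression imputation does not remove MNAR bias. The third shows that the harm depends on the mechanism differing by arm.

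**The case against.** Several points against a stronger reading are sound.

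- **A reader might infer that the wording biases the result by 12% to 39%.** It does not. That range is residual MNAR bias, and correctly specified multiple imputation under MAR would leave it too. It also assumes the whole departure falls in one arm, and the 10% and the 0.3 to 1.0 SD are not from the article.
- **Misrouting MAR data may do little harm at day 7.** If the undefined method is monotone imputation, such data still receive an MAR-based method. The planned model also adjusts for baseline: in a separate simulation with missingness depending on arm and baseline (15% missing), the complete-case ANCOVA gave −0.255, the true value.
- **A reader might infer that the article's own follow-up pattern rules out monotone methods.** The example in 'Withdrawal', a missed 3-month visit followed by a 12-month one, concerns secondary time points. With baseline observed and only day 7 missing, the pattern is monotone.
- **A reader might conclude that an MAR result would be reported under an MNAR label.** That rests on reading an undefined word in permissive text. The secure criticism is that the term is undefined and its natural reading does not serve the purpose.
- **Blinding limits steering.** Under 'Randomisation, allocation, and concealment', all but the dispensing pharmacist stay blind until the analysis ends. Reasons for missingness are also recorded. Both help, but neither fixes the method in advance or makes MAR distinguishable from MNAR.
- **Five imputations is a stated minimum.** No harm from it has been shown. The number of imputations, and whether to impute by arm, are secondary choices that an analysis plan can settle.

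An analysis plan not shown here may also be better. The point still stands, because the article does not leave the rule open: it states one, and a plan that followed it would inherit the errors.

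**Conclusion.** The concern holds, limited to three faults: the gloss on MAR describes MCAR; the choice between branches rests on a distinction that observed data cannot make; and the MNAR branch names an undefined method that, on its natural reading, still assumes MAR. The first two stand on the text alone. The third depends on that reading, though the lack of a definition does not. Together they leave the intent-to-treat day-7 comparison without a missing-data method fixed beforehand and without a genuine MNAR sensitivity analysis.

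The size of any harm cannot be taken from the document. The shift of 0.03 to 0.10 SD is an assumed range for what such an analysis might reveal when the departure is confined to one arm. It should not be cited as the cost of the wording.

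**What to change.** Amend the section on missing or incomplete data before the data are inspected:

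1. Delete the gloss that equates MAR with absence of pattern, and delete the reference to *monotonistic* methods.
2. Prespecify one primary approach valid under MAR, to be used whatever pattern is observed: either multiple imputation with arm, baseline composite, the stratification factors and other recorded predictors in the model, or an equivalent likelihood-based model.
3. Prespecify an MNAR sensitivity analysis of the day-7 contrast, by delta adjustment or tipping point, to be run regardless of how the missing data look. Allow the shift to differ between arms, since that is where the contrast is vulnerable.

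The examination of missing-data patterns and the recording of reasons can stay as description and as help in choosing plausible shifts. They should no longer select the method. The cost is a change of wording and a little extra programming, with no change to data collection.
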